## Methods

2

### Design

2.1

This controlled, naturalistic, longitudinal cohort study will follow participants over 18 months of treatment to assess recovery outcomes in patients with SMI-PD across three settings: FACT, AMBIT-PD, and AMBIT informed-MBT. A naturalistic design was chosen to enhance ecological validity and generalizability, allowing treatment to reflect real-world practice rather than rigid protocols. Unlike a randomized controlled trial (RCT), which prioritizes internal validity, this approach better captures treatment effectiveness in complex, real-life settings where patient motivation—key to therapeutic success— will not be affected by randomization (40–43). Since participants must have already been in mental health care for at least two years (6–8), altering their current care for the sake of an RCT may be unethical and disruptive. The flexibility of the AMBIT approach, which focuses on restoring trust and adapting to individual needs, would also be compromised by a rigid study design, potentially increasing epistemic mistrust and disengagement (42). A naturalistic design minimizes exclusion due to strict criteria and reduces drop-out, leading to more complete data. However, the absence of randomization does increase the risk of bias from unknown confounders, which will be considered in the analysis (40, 42–44).

### Participants

2.2

The study sample will consist of 160 patients with SMI-PD receiving care at GGZ Rivierduinen and GGZ Altrecht, mental health facilities in the Netherlands. 40 patients will be recruited at the FACT teams of Altrecht (FACT-ALT), 40 patients at the FACT teams of GGZ Rivierduinen (FACT-RIV), 40 patients at the AMBIT-PD teams of Altrecht (AMBIT-PD-ALT) and 40 patients at the AMBIT informed-MBT team of Rivierduinen (AMBIT-MBT-RIV). Participants will be recruited via their principal therapist in each of the participating teams when they meet inclusion criteria. Eligibility of each participant will be assessed before recruitment of a participant.

Participants are eligible if they 1) are 18 years of age or older, 2) are willing and able to give informed consent, 3) have a present diagnosis of a PD meeting DSM 5 criteria, 4) meet the criteria of SMI (5, 7, 8). This includes having a persistent psychiatric disorder that requires care and treatment, having undergone at least two years of treatment without achieving functional recovery (GAF ≤ 50), and experiencing impairment in social and/or societal functioning, such as difficulties in at least two areas of life, including financial issues, educational or occupational challenges, housing problems, relationship issues, substance abuse, or school/work difficulties. The dysfunction must be caused by or result in a psychiatric disorder, and coordinated care from professional caregivers in care networks is necessary to implement a treatment plan.

Participants are excluded from participation in this study if they 1) do not master the Dutch language, 2) are significantly under the influence of substances and are unwilling to detoxify elsewhere, or 3) if they have an intellectual impairment (IQ < 80, based on the Wechsler Adult Intelligence Scale).

#### Sample size calculation

2.2.1

Based on previous studies reporting reductions in overall psychiatric symptoms following MBT, with effect sizes ranging from 0.59 to 1.79 (38), an *a priori* power analysis was conducted in G*Power 3.1.9.6 to determine the optimal sample size. Assuming a medium effect size (f = 0.25), a significance level of α = 0.05, and 90% power in a repeated-measures ANOVA with three measurements across three conditions, a total of 135 participants would be required to detect an existing effect. Accounting for an anticipated dropout rate of approximately 20%, a final sample size of 162 participants will be recruited to maintain sufficient power.

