#### Feasibility

2.2.2

To map the feasibility of participant recruitment, we rely on the standard guideline of care for personality disorders (45). It is estimated that approximately 30% of the FACT teams meet the criteria for SMI-PD. GGZ Rivierduinen location Leiden has 4 FACT teams. Altrecht location Utrecht has 9 FACT teams. Each team has at least 200 clients in care on a yearly basis. Therefore, approximately 60 clients per FACT team are likely to meet the inclusion criteria of the study, which amounts to around 780 clients (45). As the study is observational in nature and only minimally burdensome for participants (questionnaires), and since we plan to provide a generous participation fee of 30 euros per measurement, we think it is reasonable to expect that around 10% of the clients will consent to participate. From previous naturalistic research (46), it was found that a vast majority (87%) of this target group was willing to participate in research. Rivierduinen has one AMBIT informed-MBT team, whereas Altrecht has five, who each treat 200 to 250 clients, nearly all of whom meet the inclusion criteria of the study, amounting to around 1000 likely eligible participants. Since this also concerns naturalistic research, we are confident that recruiting 80 participants at Rivierduinen and 80 at Altrecht is feasible.

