#### Multilevel (mixed) model analysis

3.1.3

Multilevel (mixed) model analysis will be conducted to compare outcomes for both conditions on the OQ-45.2, with baseline scores (T0), scores after 9 months (T1), and at the end of treatment after 18 months (T2) as dependent variables and treatment (FACT or AMBIT) as independent variable. The different levels for the multilevel (mixed) model analysis will be: 1) participant, 2) measurement wave, 3) outcome measure, and 4) location of sampling. A multilevel (mixed) model analysis uses all data and contributes to power in the analysis in contrast to case wise deletion for missing data.

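### The 90% power in 2.2.1 makes no allowance for clustering by treating team; FACT versus AMBIT power falls below 90% once the team ICC exceeds about 0.01, under stated assumptions

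*Protocol article*

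**What the plan says.** Section 2.2.1 reports a completed G*Power calculation at f = 0.25 and alpha = 0.05. Its test, power and result read: "90% power in a repeated-measures ANOVA with three measurements across three conditions, a total of 135 participants would be required to detect an existing effect". The only inflation is for about 20% dropout. No team, ICC or design effect is mentioned.

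Section 2.2 sets four quotas of 40, 160 patients in all. One of them is "40 patients at the AMBIT informed-MBT team of Rivierduinen (AMBIT-MBT-RIV"), with team in the singular. Section 2.2.2 confirms the count: "Rivierduinen has one AMBIT informed-MBT team, whereas Altrecht has five". It also gives 4 FACT teams at Rivierduinen and 9 at Altrecht. Section 2.5.1.2 confirms five AMBIT-PD teams.

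Section 3.1.3 compares FACT with AMBIT on the OQ-45.2 in a multilevel model: "The different levels for the multilevel (mixed) model analysis will be: 1) participant, 2) measurement wave, 3) outcome measure, and 4) location of sampling". Location is the only grouping above the patient that is named.

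**The concern.** Teams deliver the treatments. In the AMBIT informed-MBT team the standard programme includes group therapy one to three times a week, and the team has weekly intervision (2.5.1.1). Patients who share therapists and groups can have correlated outcomes. When they do, the difference between the arms has a larger variance than a calculation for independent patients assumes.

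The protocol accepts nesting in the analysis (3.1.3) but does not carry it into the sample size (2.2.1). Half of the AMBIT arm sits in one team, so this is where the effect is concentrated. At stake is how a null result is read: readers would rely on a 90% that may not have been available.

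**Working it through.** **Inputs from the article.** f = 0.25, alpha = 0.05, three measurements, three conditions, 135 evaluable patients, 20% dropout (2.2.1); quotas 4 x 40 (2.2); teams 4 + 9 FACT, 5 AMBIT-PD and 1 AMBIT informed-MBT, so 19 at most (2.2.2).

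**Assumptions, not in the article.** The correlation between repeated measures is 0.5. The ICC is on the scale of the patient's mean over measurements, range 0 to 0.10. Recruitment is even over teams within each quota, and the 20% loss is even over teams. f = 0.25 is carried over to the two-arm comparison.

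**Step 1: the plan's own figure.** For the between-group test, lambda = f² x N x m / (1 + (m - 1) x rho). With N = 135, m = 3 and rho = 0.5 this is 0.0625 x 135 x 3 / 2 = 12.66. On 2 and 132 df the power is 0.893. A correlation of about 0.48 brings 135 to 90%. So 135 is approximately reproduced, as a figure for independent patients.

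**Step 2: design effect.** 160 x 0.80 = 128 analysed, 64 per arm. Team sizes after loss are 1 x 32 and 5 x 6.4 in AMBIT, and 4 x 8 and 9 x 3.56 in FACT. The slope per arm is the sum of m(m - 1) divided by the sum of m, where m is team size:

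- AMBIT: (32 x 31 + 5 x 6.4 x 5.4) / 64 = 15.5 + 2.7 = 18.2
- FACT: (4 x 8 x 7 + 9 x 3.56 x 2.56) / 64 = 3.5 + 1.3 = 4.8
- Mean for the two-arm contrast: 11.5

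The design effect is about 1 + 11.5 x ICC. The single team contributes 15.5 / 2 = 7.75 of the 11.5, about two thirds.

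**Step 3: FACT versus AMBIT, 128 analysed.** Without clustering, lambda = 0.0625 x 128 x 1.5 = 12.0. With clustering it is 12.0 divided by the design effect. At ICC 0.05, for example, 12.0 / 1.57 = 7.6.

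| ICC | Design effect | Effective N | Power, patient df (1, 126) | Power, team df (1, 17) |
|---|---|---|---|---|
| 0 | 1.00 | 128 | 93% | 90% |
| 0.01 | 1.11 | 115 | 90% | 87% |
| 0.02 | 1.23 | 104 | 87% | 84% |
| 0.05 | 1.57 | 81 | 78% | 74% |
| 0.10 | 2.15 | 60 | 65% | 61% |

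**Step 4: the three-condition test of 2.2.1, 128 analysed.** A team of n patients gets weight 1 / (ICC + (1 - ICC)/n), and weights are summed within each condition. Lambda is 1.5 times the weighted sum of squared deviations of the condition means, scaled to f = 0.25. Four patterns were tried: both AMBIT conditions differ from FACT, AMBIT-PD only, AMBIT informed-MBT only, and a linear order.

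Example at ICC 0.05 with only AMBIT informed-MBT differing: the weights are 52.1 (FACT), 25.2 (AMBIT-PD) and 12.5 (AMBIT informed-MBT). Lambda is about 5.4 and power on 2 and 125 df is 53%.

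Over all four patterns power is 88% at ICC 0, 79-85% at 0.01 and 53-76% at 0.05. The 88% at ICC 0 comes from dropout alone: 2.2.1 multiplies 135 by 1.2 to get 162, whereas 135 / 0.80 = 169, and 160 leaves 128. That shortfall is separate from clustering.

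**Step 5: the single team.** Its 32 analysed patients count as 32 / (1 + 31 x ICC), which is about 24, 13 and 8 at ICC 0.01, 0.05 and 0.10.

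**The case against.** **No ICC is given.** A reader might infer that 90% is not reached under any plausible team correlation. The documents do not support that. With 128 analysed and patient df, the two-arm test still has 90% at ICC 0.01. With the full 135 evaluable it has 92% at 0.01 and 89% at 0.02. The loss has to be stated as conditional.

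**The choice of test matters.** Section 2.2.1 does not say whether f refers to the between-group effect or to the group-by-time interaction. Under G*Power's default interaction definition there would be a large reserve: power is still 98% at an effective N of 61. But that option needs only 45 patients, so it does not explain the stated 135. The alternative interaction definitions need 126 or 129, and they too treat patients as independent. Conversely, power from some other test, such as a baseline-adjusted comparison at a single time point, should not be set directly against the protocol's 90%, because 2.2.1 does not describe such a test.

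**The ICC scale.** Section 3.1.3 uses T0, T1 and T2. If the effect is read as change from baseline, stable team differences cancel and only differences in change between teams count. This stands, and it is why the scale of the ICC must be named.

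**Confounding rather than precision.** One team is the whole AMBIT informed-MBT condition, so its team effect cannot be separated from the condition, and more patients from that team would not help. This also stands and belongs in the text. The general caveats on confounding in 2.1 and the Discussion do not mention it.

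**Nothing is miscalculated.** True. The fault is an assumption that the design breaks, not an arithmetic error.

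**Conclusion.** The point holds in conditional form. The 135 patients and 90% power apply to independent patients, and the quotas make that assumption doubtful. Any positive ICC lowers the power. Its size rests on the assumptions listed in the working. On these, two-arm power with patient df passes below 90% at an ICC of about 0.01 and is about 78% at 0.05. With 17 team df it is about 90% at ICC 0 and below 90% already at 0.01. The three-condition test is below 90% at every ICC with 128 analysed, partly because of the dropout shortfall. The loss is small at an ICC of 0.01 and material at 0.05. The documents do not show which applies.

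**What to change.** Keep 160 patients. In 2.2.1:

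- Say that the 90% holds only if patients are independent.
- Replace it with power over a stated ICC range for the FACT versus AMBIT comparison of 3.1.3, computed from the actual quotas. Name the test, the effect definition, the repeated-measure correlation and the scale of the ICC.
- State that the single AMBIT informed-MBT team drives most of the loss, and that its team effect cannot be separated from that condition.
- Aim for even recruitment over the five AMBIT-PD and 13 FACT teams. For fixed quotas, equal team sizes give the smallest design effect.

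The cost is one calculation, a few sentences and some attention to how recruitment is spread. No extra patients are needed. The downside is that the stated power becomes less favourable.

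### The 20% dropout allowance is miscalculated (162 instead of 169), the recruitment target is 160 elsewhere, and the stated 90% power is for a three-condition test rather than the two-group primary comparison

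*Protocol article*

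**What the plan says.** Section 2.2.1 (Sample size calculation) sets the inputs, "Assuming a medium effect size (f = 0.25), a significance level of α = 0.05, and 90% power", and gives the requirement as "90% power in a repeated-measures ANOVA with three measurements across three conditions, a total of 135 participants would be required". It then adds the dropout allowance: "Accounting for an anticipated dropout rate of approximately 20%, a final sample size of 162 participants will be recruited to maintain sufficient power".

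The recruitment plan elsewhere has a different total. Section 2.2 (Participants) states: "The study sample will consist of 160 patients with SMI-PD receiving care at GGZ Rivierduinen and GGZ Altrecht", made up of four groups of 40. The abstract also gives 160, and section 2.2.2 (Feasibility) plans 80 at each institution.

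The primary model in section 3.1.3 has "treatment (FACT or AMBIT) as independent variable", which is a comparison of two conditions.

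**The concern.** Three figures that should agree do not.

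- The dropout allowance adds 20% to the required number. It should divide that number by the 80% expected to remain.
- The result, 162, differs from the 160 planned everywhere else in the article.
- The power calculation is for three conditions, whereas the primary model has two.

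The sample size section is where a reader looks to learn what the study can detect. As written, the 90% belongs neither to the number expected to complete the study nor to the primary comparison.

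**Working it through.** **Inputs from section 2.2.1:** f = 0.25, α = 0.05, target power 90%, three measurements, three conditions, 135 required, dropout about 20%, 162 to recruit. **From the abstract, 2.2 and 2.2.2:** 160 to recruit.

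**Step 1: the plan's 162.** 135 × (1 + 0.20) = 162, an exact match.

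**Step 2: the number that keeps 135 after 20% loss.** 135 / (1 − 0.20) = 168.75, so 169.

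**Step 3: what each target delivers.**

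| Recruited | Left after 20% loss | Shortfall against 135 | Dropout at which 135 remain |
|---|---|---|---|
| 162 | 162 × 0.8 = 129.6 | 5.4 | 1 − 135/162 = 16.7% |
| 160 | 160 × 0.8 = 128 | 7 | 1 − 135/160 = 15.6% |
| 169 | 169 × 0.8 = 135.2 | none | 20.1% |

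**Step 4: which test lies behind 135.** The article gives neither the effect tested nor the correlation ρ between waves, so both are assumptions here. For the between-groups effect with k groups and m measurements, the noncentral F has

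λ = f² · N · m / (1 + (m − 1)ρ), with df = (k − 1, N − k).

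With k = 3, m = 3, ρ = 0.5 and N = 135, λ = 0.0625 × 135 × 3 / 2 = 12.66 and power is 0.893. Power at 135 is exactly 0.90 when ρ is about 0.478. Other readings fit 135 less well: the group-by-time interaction at ρ = 0.5 needs 45, the interaction on the alternative (Cohen-style) effect-size scale needs 126 to 129, and a single measurement needs 207. The between-groups test with ρ near 0.5 is therefore the working assumption.

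**Step 5: power of the three-condition test at the numbers actually left.**

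| Completers | ρ = 0.5 | ρ = 0.478 |
|---|---|---|
| 135 | 0.893 | 0.900 |
| 129.6 (162 recruited) | 0.879 | 0.887 |
| 128 (160 recruited) | 0.875 | 0.883 |

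The dropout slip and the lower target together cost just under 2 percentage points.

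**Step 6: the same model for the two conditions of section 3.1.3.** Put k = 2 and keep f = 0.25, m = 3 and ρ = 0.5. At N = 128, λ = 0.0625 × 128 × 3 / 2 = 12.0 with df = (1, 126), and power is 0.930 (0.935 at ρ = 0.478). In this model 90% needs 116 completers, so 128 − 116 = 12 participants, or six matched pairs, could be lost before power falls below 90%.

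**The case against.** The strongest reply is that little is at stake. The dropout rate is only approximate, 160 against 162 is two people and fits rounding to four groups of 40, and power moves by less than 2 points. On the alternative interaction scale in step 4, 128 completers would give 89.8%, almost no shortfall. All of this holds and limits the severity. It does not make 135 × 1.2 a 20% allowance, and the article still gives two different recruitment totals.

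A second reply is that dropouts are not wholly lost. Section 3.1 imputes missing data, and the mixed model in 3.1.3 uses every available measurement, so counting completers overstates the loss from dropout. That also holds. Against it, section 3.1.2 removes pairs that match poorly on the propensity score, and 2.2.1 makes no allowance for this. Section 2.9 says recruitment goes on until the needed number is reached, but it gives no figure and so does not settle the conflict.

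A third reply is that three conditions are part of the design: section 2.1 names three settings. That is correct, and a pooled two-group primary test is compatible with it. The power figure is still not the one for that test.

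Two stronger readings are tempting and are not supported:

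- A reader might infer that the FACT-versus-AMBIT comparison misses 90%. An unadjusted two-group test of T0-to-T2 change with d = 0.5, correlation 0.5 and 64 completers per group has about 80% power. The plan does not state that test: section 3.1.3 uses all three waves in a mixed model. Adjusting the same contrast for baseline gives about 90%, and the plan's own type of calculation gives about 93%. This spread comes from choices the article does not document, so it shows no failure.
- A reader might count the unstated correlation and tested effect as defects. A journal article commonly leaves such settings to the full protocol, which is not shown here.

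**Conclusion.** The point holds as a minor to moderate error in the stated sample size. The 162 is wrong for a 20% dropout allowance; the figure is 169. The 160 planned elsewhere leaves 128, which is 7 below the plan's own requirement. On the three-condition calculation, power is then about 87.5 to 88% instead of 90%, assuming a between-groups test, a correlation near 0.5, and no contribution from participants who drop out.

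The 90% also does not describe the primary two-condition test. With f = 0.25 carried over to two groups and the same assumptions, that test has about 93% at 128 completers, before any loss to matching. The article therefore quotes the wrong figure for its primary comparison, but nothing in it shows that comparison to be underpowered.

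**What to change.** Use one recruitment number in the abstract and in sections 2.2, 2.2.1 and 2.2.2. The simplest course is to keep 160, state that 20% dropout leaves about 128 completers, and replace the 90% with the power for that number on the FACT-versus-AMBIT comparison of section 3.1.3. If the sponsor prefers to keep the 135 requirement at 20% dropout, the recruitment figure is 169.

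Keeping 160 is a rewording only. It needs no extra patients and changes neither the design nor the analysis. Choosing 169 means nine more participants than the 160 now planned.

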#### Feasibility

2.2.2

To map the feasibility of participant recruitment, we rely on the standard guideline of care for personality disorders (45). It is estimated that approximately 30% of the FACT teams meet the criteria for SMI-PD. GGZ Rivierduinen location Leiden has 4 FACT teams. Altrecht location Utrecht has 9 FACT teams. Each team has at least 200 clients in care on a yearly basis. Therefore, approximately 60 clients per FACT team are likely to meet the inclusion criteria of the study, which amounts to around 780 clients (45). As the study is observational in nature and only minimally burdensome for participants (questionnaires), and since we plan to provide a generous participation fee of 30 euros per measurement, we think it is reasonable to expect that around 10% of the clients will consent to participate. From previous naturalistic research (46), it was found that a vast majority (87%) of this target group was willing to participate in research. Rivierduinen has one AMBIT informed-MBT team, whereas Altrecht has five, who each treat 200 to 250 clients, nearly all of whom meet the inclusion criteria of the study, amounting to around 1000 likely eligible participants. Since this also concerns naturalistic research, we are confident that recruiting 80 participants at Rivierduinen and 80 at Altrecht is feasible.

### Measures

2.3

#### Main Study parameter/endpoint

2.3.1

The Outcome Questionnaire (OQ-45.2) (47, 48) is a self-report measure designed to monitor overall psychological distress and psychological functioning. The OQ-45.2 consists of 45 items divided into three subscales: subjective distress (intra-psychological functioning), interpersonal functioning, and social role functioning. Items are rated on a 5-point Likert scale ranging from 0 (*never*) to 4 (*almost always*), yielding a total score between 0 and 180. Higher scores indicate greater psychological distress and functional impairment. Total and subscale scores demonstrate adequate reliability and validity (48).

#### Secondary study parameters/endpoints

2.3.2

##### Demographic variables and clinical data

2.3.2.1

Several clinical and demographic data will be collected, including sex, age, age of onset of self-harm, education, vocation, days spent in hospitalization due to psychiatric complications, receiving involuntary care under the Compulsory Mental Health Care Act (Wet verplichte geestelijke gezondheidszorg, Wvggz) (49) and number of suicide attempts or self-harm incidents.

##### Personality functioning

2.3.2.2

The Severity Indices for Personality Problems-Short Form (SIPP-SF) (50) is a self-report questionnaire designed to assess maladaptive personality functioning over the past 3 months. The SIPP-SF consists of 60 items rated on a 4-point Likert scale ranging from 1 (strongly disagree) to 4 (strongly agree). The items measure maladaptive personality functioning across five domains: 1) Self-control, 2) Identity integration, 3) Relational capacities, 4) Responsibility, 5) Social concordance. Higher scores in each domain indicate more adaptive functioning, whereas lower scores reflect greater maladaptive traits. The SIPP-SF is a valid and reliable measure for maladaptive personality characteristics (50).

